### Study procedure

All eligible participants will run over a 12-week integrated exercise and sleep intervention. A trained GESO research assistant will contact potential participants via face-to-face meeting, telephone call, or online platforms (e.g., voice call or video call) to introduce the study, discuss participation, answer questions, and determine eligibility. Then, eligible participants who express willingness to join will then provide a signed written informed consent. For participants contacted remotely (via telephone or online) will sign the informed consent form during the baseline assessment.

To minimize participant burden, we will deliberately distribute all assessments across the study period. Specifically, subjective measurements (i.e., questionnaires and scales) will be collected at the beginning of the first week. Then, researchers will equip with the ActiGraph accelerator device (GT3X) and give usage instructions for each participant. After a one-week monitoring period, participants will be required to return the device. The saliva sample and resting-state EEG will be collected within one week after allocation and post-intervention (12-week) according to participant availability. Notably, the EEG and saliva collection are part of an optional sub-study on mechanisms. For those who consent to this sub-study, we offer flexible scheduling and transportation assistance to facilitate participation. Participation is voluntary and does not affect involvement in the main trial or compensation. Other proactive strategies in order to enhance engagement and minimize dropout include a dedicate research assistant to maintain weekly contact, offering a highly flexible schedule, providing small, tiered compensation after each major time point, and giving personalized guidance and feedback on participants’ health conditions and improvements.

### Randomization and blinding

Initially, all six communities will begin in the control phase. Subsequently, two communities will be randomly allocated to the 12-week intervention period, followed by two other communities 12 weeks later, and the final two communities 12 weeks after that. Trial randomization will be performed by an independent researcher not otherwise involved in the study. Each community will be notified of its own transition date after recruiting first participant but will not be notified of the transition dates of other communities. Details of the randomization schedule are given in Fig. 1.

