**Fig. 1 Fig1:**
[figure not shown]
Randomization schedule

As this is an open-label study, both participants and intervention deliverers will be aware of allocation. Participants will be informed that they will receive a 12-week home-based exercise and sleep health intervention with mobile phone support. However, the participating communities will not be aware of the allocation sequences for themselves or others. We will also blind the assessors (data collectors) and statisticians to group allocation.

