There are some limitations in this study. First, although the proposed SW-CRT design has several advantages over parallel group RCTs, it is not as methodologically rigorous as a true cluster-randomized design, and inevitably brings challenges in recruitment and implementation [63], possibly create time contamination and complexity of analysis. Nevertheless, recruitment of the GESO project will be community-based participatory research, that is, community organizations will contribute to both the recruitment and implementation phases of the project through activities such as promotion and participant mobilization, assistance with follow-ups, and the provision of venue resources. Second, this study design precludes the effectiveness evaluation of the core active components or optimal strategies compare with overall intervention package. For instance, it cannot determine the optimal sequence for delivering exercise versus sleep intervention or evaluate the potential of alternative delivery agents (e.g., virtual agents, primary care nurses, non-specialist assistants). Future studies could employ a sequential multiple assignment randomized trial (SMART) design to optimize strategies and test such alternative agents. Third, the collection of EEG data is optional and require additional time (e.g., commuting time) for participants, which is likely to result in a subsample of participants with greater motivation or better physical mobility. Therefore, the findings of EEG should be interpreted as preliminary and may not generalize to the full study population. Finally, culturally and linguistically diverse residents are likely to be underrepresented, due to constraints in financial and human resources, which may limit the generalizability of the results. Further multicenter studies recruiting a wider range of older adults with larger sample sizes are recommended.

In conclusion, the present study will advance the extant knowledge about effectiveness, acceptability, and cost-effectiveness of an integrated exercise-sleep intervention, with a specific focus on older adults with depression in community settings. The findings will contribute to providing a more cost-effective, evidence-based, and scalable lifestyle intervention for this population.

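### The protocol both discloses and withholds each community's own transition date, and disclosure after the first recruit leaves most recruitment unconcealed

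*Protocol article*

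**What the plan says.** All statements are in the protocol article.

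- **Randomization and blinding, disclosure.** All six communities start in the control phase, and two cross over at each of three steps 12 weeks apart. "Each community will be notified of its own transition date after recruiting first participant"; other communities' dates are withheld from it.
- **Randomization and blinding, text under Fig. 1.** "the participating communities will not be aware of the allocation sequences for themselves or others". The trial is open-label: "both participants and intervention deliverers will be aware of allocation". On masking: "We will also blind the assessors (data collectors) and statisticians to group allocation".
- **Sequence generation.** "Trial randomization will be performed by an independent researcher not otherwise involved in the study".
- **Study procedure.** A trained research assistant approaches candidates and determines eligibility. People contacted remotely "will sign the informed consent form during the baseline assessment". For the optional sub-study, "The saliva sample and resting-state EEG will be collected within one week after allocation".
- **Participants and recruitment.** Entry requires a PHQ-9 score of at least 5. The same scale gives the primary outcome (Measurement of outcomes).
- **Table 1.** Eligibility screen, informed consent and allocation share the enrolment column, which precedes baseline (T0).
- **Discussion.** "community organizations will contribute to both the recruitment and implementation phases of the project", including promotion and participant mobilisation.

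**The concern.** There are two linked problems.

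First, the protocol gives opposite instructions on whether a community learns its own place in the rollout. Staff cannot follow both.

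Second, the more operational of the two instructions ties disclosure to the first recruit. In a cluster trial, concealment has to last until individuals have been identified, have consented and have been measured at baseline. Otherwise those who recruit, and those who decide whether to join, can act on the start date. A community due to start soon may draw people who are motivated or currently unwell, and one due to start months later may draw people content to wait. Sequence could then be associated with who is enrolled and how their symptoms would have changed without treatment. A cluster effect removes stable level differences and a common period effect removes shared trends. Neither removes a course over time that differs by sequence.

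**Working it through.** **1. Are the two statements compatible?**

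| Question | Disclosure sentence | Sentence under Fig. 1 |
|---|---|---|
| Does a community know other communities' timing? | No | No |
| Does a community know its own timing? | Yes, after its first recruit | No |

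The three steps are fixed and 12 weeks apart, so knowing the date means knowing the sequence. The second sentence covers the community itself and has no time limit. The two agree on other communities and conflict on the community's own timing.

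**2. The plan's own total.** Inputs from Sample size: 6 clusters, 22 participants per community, 20% dropout.

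- 6 × 22 = 132
- 132 / (1 − 0.20) = 165, which matches the stated total

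**3. Share of recruitment open to foreknowledge if the disclosure sentence governs.** One participant in each of six communities is recruited before disclosure can occur.

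- Inflated total: (165 − 6) / 165 = 159 / 165 = 96.4%
- Before dropout inflation: (132 − 6) / 132 = 126 / 132 = 95.5%
- Average per community: 165 / 6 = 27.5, of whom 26.5 come after the first
- If the date is released only after recruitment closes: 0%

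The first two percentages are ceilings. They assume notice immediately after the first recruit, and the protocol gives no interval.

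**4. Is there a route from foreknowledge to selective enrolment?**

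- The notified party is the community, and community organisations help to promote the trial and mobilise participants.
- Masking is stated for data collectors and statisticians. The assistant who determines eligibility is not said to be unaware of the sequence.
- Entry depends on a self-reported score, so who comes forward and how they answer can vary with what they expect.
- People contacted remotely sign only at the baseline assessment, which Table 1 places after allocation. They could still decline once the timing is known. Table 1 itself lists consent at enrolment, and the Ethical approval section places written consent for all participants at baseline, so the consent step also needs one fixed position.
- The independent randomiser protects generation of the sequence. It does not keep the sequence concealed while recruitment continues.

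**5. Can the bias be sized?** No. That would need the difference between sequences in the kind of person enrolled, and the protocol gives nothing from which to derive it.

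**The case against.** **Regression to the mean.** A reader might infer that regression to the mean after selection at PHQ-9 ≥ 5 shows a bias that is a large part of the 2.0-point difference used for sample size. Take an assumed population mean of 4 to 6, SD 4 and retest reliability 0.7 to 0.8, none of which is in the protocol. A simulated untreated retest then falls by about 0.5 to 1.1 points, and 15% to 28% score below 5. But that is the total fall, and it occurs in every sequence whether or not anyone knows the date. Only a difference between sequences can bias the comparison. If one sequence is set at mean 4 and another at mean 6, the falls differ by 1.05 − 0.70 ≈ 0.36 points (reliability 0.7) or 0.72 − 0.47 = 0.25 (reliability 0.8), before any modelling, and the more severely affected group falls less. Other assumed selection patterns give other values. These figures illustrate the issue and do not estimate the bias.

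**Planned adjustment.** Statistical analyses includes individual-level effects, the baseline value of the outcome, baseline covariates and community-level covariates, and a sensitivity analysis adjusts for baseline severity. This stands: measured severity differences would be largely addressed. Selection on unmeasured traits such as motivation or expected course would not.

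**Nearly everyone recruited with the date known.** A reader might state 96% as fact. The text does not support that. It depends on the disclosure sentence governing and on prompt notice. If the sentence under Fig. 1 governs, there is no foreknowledge at community level.

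**Weak links in the route.** Eligibility is determined by research staff, not by the communities, and nothing says that communities pass the date to candidates before consent. Baseline after allocation is harmless if allocation is concealed. Saliva and EEG belong to an optional, exploratory sub-study and do not bear on the primary outcome. All of this is fair. It shows that selective recruitment is possible under the text, not that it will happen.

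**Conclusion.** The contradiction is certain on the wording. The concealment weakness is conditional: if the disclosure sentence is followed, up to 159 of 165 participants (96.4%) could be recruited with their community's start date known. This assumes notification straight after the first recruit and enrolment at the planned total. The protocol describes a plausible route to selective recruitment by sequence and states no safeguard for the people who recruit. With only two communities per sequence, chance balance gives little protection. Baseline adjustment would reduce the resulting bias without removing the part due to unmeasured selection. Neither the size nor the direction of that bias can be derived from the protocol. Fig. 1 was not available, but a schedule could not make both sentences true.

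**What to change.** Replace both sentences with one rule: the independent researcher withholds a community's transition date from that community, from recruiters and from prospective participants until that community's recruitment, written consent (including remote contacts) and baseline PHQ-9 are complete. Amend Table 1 so that disclosure of allocation follows these steps, and bring the consent statements in Study procedure and Ethical approval into line with it.

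The cost is small: a wording change, shorter notice for communities, and recruitment that must close in a community before its date is released. The change has to be made before recruitment, because concealment cannot be restored in the analysis.

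It is not necessary to complete every baseline measure in all six communities before the sequence is generated. For the last communities, that could separate the saliva and EEG baseline from the start of intervention by up to two further 12-week steps and weaken their pre/post comparison. The timing of that optional baseline need not change.

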**Fig. 1 Fig1:**
[figure not shown]
Randomization schedule

As this is an open-label study, both participants and intervention deliverers will be aware of allocation. Participants will be informed that they will receive a 12-week home-based exercise and sleep health intervention with mobile phone support. However, the participating communities will not be aware of the allocation sequences for themselves or others. We will also blind the assessors (data collectors) and statisticians to group allocation.

### Interventions

Based on the literature review [37–39] and our previous study, a preliminary integrated intervention framework was developed for older adults with depression. The intervention consists of two core components: a multi-component exercise and sleep hygiene education (SHE). These components are theoretically and practically synergistic and are delivered in a coordinated manner over the 12-week period, supported by behavioral activation (BA) techniques to facilitate adherence and behavior change [40, 41].

Exercise component: The exercise program is primarily based on the Otago Exercise Program [42] and will be refined in consultation with sports experts. It is designed as three time-stratified regimens to align with circadian rhythms and daily routines:Morning regimen (10 minutes): Focusing on low-intensity activation and circadian entrainment upon waking, involving dynamic stretching and light exposure.Afternoon regimen (20 min): Constituting the core exercise session, including low to moderate intensity aerobic exercise, resistance training, and balance training. Exercise intensity will be standardized using the Borg Rating of Perceived Exertion (RPE 6–20) scale. Participants will be trained to maintain an RPE between 11 and 16 (low to moderate intensity) during the aerobic session [43, 44].Pre-sleep regimen (15 min): Aiming at promoting physiological and cognitive relaxation within 1 h of bedtime, primarily consists of flexibility training. Participants will also be encouraged to incorporate brief ‘zero-time’ activities throughout the day to interrupt sedentary behavior or physical inactivity.Sleep component: The SHE is based on established sleep hygiene recommendations [45]. It comprises structured behavioral advice concerning modifiable lifestyle and environmental factors associated with sleep quality [11]. Key education topics include regulating sleep-wake schedules, optimizing the bedroom environment (e.g., reducing light and noise), scheduling napping, managing caffeine and alcohol intake, and establishing a pre-sleep wind-down routine.

The two components are integrated into a unified, home-based intervention package. BA techniques including goal setting, activity scheduling and monitoring, reinforcement, and relaxation training, will be incorporated into the 12-week intervention implementation to support the adoption and maintenance of the integrated exercise-sleep intervention. In the control phase, participants will be advised to maintain their normal daily activities and will only receive minimum contact (once per week) to reduce the pre-intervention attrition. The final integrated intervention will be refined through a preliminary test with 20 participants based on rationale about feasibility. Detailed description of the intervention, according to the template for intervention description and replication (TIDieR) checklist [46], is provided in Supplementary 2.

### Data management plan

Data will be securely stored on offline computers and in secure locations. Access to participant data will be restricted according to researcher role. Participant confidentiality will be maintained at all times except in cases where significant risk of harm to self or others is identified.

### Sample size

Power calculation was performed using the PASS software module ‘Tests for Two Means in a Stepped Wedge Cluster Randomized Design’. Key input parameters were derived from a similar previous study [47], which reported a mean reduction in depressive symptom of 4.0 in intervention group compared to 2.0 in control group among community-dwelling older adults with depression. Based on our stepped-wedge design with 6 clusters, 2 clusters crossing over per sequence, an intra-cluster correlation (ICC) of 0.1, a planned sample size of 22 per community, a desired power of 90%, a two-side α level of 0.05, and an estimated 20% dropout rate, a total sample size of 165 participants will be required.

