### Statistical analyses

Analyses will include descriptive summaries and preliminary unadjusted comparisons between phases (control vs. intervention) and clusters. Specifically, variables within each phase or clusters will be described using descriptive statistics (means and 95% confidence intervals for normal distributed quantitative variables; medians and interquartile ranges for non-normally distributed quantitative variables).

Analyses of data from a SW-CRT requires specific methodological considerations to account for its design, including the control of secular trends (period effects) and the assessment of potential carryover effects. Guided by methodological recommendations for SW-CRTs [60], we will choose Method 3 to evaluate the intervention effects of the integrated exercise-sleep intervention. This method treats the intervention variable as a time-dependent categorical variable, comparing groups with different numbers of intervention measurements with all the control measurements. This allows us to examine whether the effect of the integrated exercise–sleep intervention varies with the length of exposure, thereby informing the time dependency of treatment effects, including potential carryover.

All models will be estimated using multilevel mixed-effects regression to account for the hierarchical structure of the data. We will first fit a two-level (time and individual levels) and a three-level (time, individual, and community levels) mixed-effects model without any potential confounders. Then, we will further adjust the selected model (based on model fit criteria) by including study period (time) as a fixed effect. Third, an adjustment will be made for the baseline value of the outcome variable and associated baseline covariates (e.g., socio-demographics, cognition), and in the fourth step, both an adjustment for the follow-up time, the baseline value of the outcome variable, and related covariates will be performed. To evaluate the time dependency of the effect of starting the intervention, an interaction term between intervention and time can be added to the model [60, 61]. Additionally, we will account for potential between-cluster variations by including relevant community-level covariates (e.g., socio-cultural characteristics and access to health services) as fixed effects in the models, if they show preliminary associations with the outcome.

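### The 90% power belongs to one constant intervention effect, but the chosen analysis estimates a separate effect for each length of exposure, and nothing links the two

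*Protocol article*

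**What the plan says.** **Sample size.** The calculation uses the module "Tests for Two Means in a Stepped Wedge Cluster Randomized Design". The effect is one difference, from "a mean reduction in depressive symptom of 4.0 in intervention group compared to 2.0 in control group", that is 2.0 points. The design is "6 clusters, 2 clusters crossing over per sequence", with ICC 0.1, 22 per community, "a two-side α level of 0.05", "a desired power of 90"%, and 20% dropout, giving 165 participants. No SD and no within-person correlation are given, and it is not said whether 22 is per period or in total.

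**Statistical analyses.** The article states that "we will choose Method 3 to evaluate the intervention effects of the integrated exercise-sleep intervention". It describes the method as coding the intervention by the number of intervention measurements received, each category being compared with all control measurements. The stated reason is: "This allows us to examine whether the effect of the integrated exercise–sleep intervention varies with the length of exposure". The same section says that a stepped-wedge analysis must control for period effects, and it adds study period as a fixed effect in the second modelling step. Its later paragraph on the intention-to-treat analysis describes the reported effect as a mean difference or odds ratio between intervention and control periods, which reads as one contrast.

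**Measurement of outcomes and Table 1.** The primary time point is 12 weeks after the start of the intervention. The PHQ-9 is listed at baseline, 6 weeks and 12 weeks, and nothing is listed after that.

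**The concern.** In a complete wedge, the constant-effect model pools every intervention cluster-period. The three sequences contribute 3, 2 and 1 such periods with two communities each: 2 × (3 + 2 + 1) = 12. Method 3 divides the same 12 among three coefficients. One period of exposure is seen in all six communities, two periods in four, and three periods in two. Each coefficient must also be separated from the period effects. The sized quantity and the analysed quantity therefore differ whatever correlation is assumed.

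Two things are at stake. A reader will take 90% as the power of the analysis the article describes, which it is not shown to be. And a null result at longer exposure, where the precision is poor, could be read as an effect that fades, although the trial was not sized to tell.

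**Working it through.** **1. The article's sample size.** 6 × 22 = 132, and 132 / (1 − 0.20) = 165. This reproduces exactly. The 90% itself cannot be reproduced, because no SD is given.

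**2. Model.** Three sequences × two communities × four 12-week periods (one control period, then three steps, from Randomization and blinding). Fixed period effects, random community effect, m = 22 per community per period (assumed), ICC = 0.1, within-person correlation ρ (assumed, 0 to 0.7). The covariance of one community's period means is

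V = SD² × [ICC·J + ((1 − ICC)/m)·(ρJ + (1 − ρ)I)],

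where J is the matrix of ones and I the identity. The variance of an effect is its diagonal element in the inverse of ΣX′V⁻¹X. Power = Φ(2.0/SE − 1.96).

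**3. Calibration to the stated 90%.** At ρ = 0 the SE of the constant effect is 0.1525 SD. For 90% power, 2.0/SE must equal 1.96 + 1.2815 = 3.2415, so SD = 2.0 / (3.2415 × 0.1525) ≈ 4.05.

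**4. Method 3 on the same layout.** With a true effect of 2.0 at every exposure length, power = Φ(3.2415/√R − 1.96), where R is the variance relative to the constant effect. At ρ = 0:

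| Effect | R | Working | Power |
|---|---|---|---|
| 1 period of exposure | 1.137 | Φ(3.040 − 1.96) | 86% |
| 2 periods | 2.366 | Φ(2.107 − 1.96) | 56% |
| 3 periods | 4.938 | Φ(1.459 − 1.96) | 31% |
| Unweighted average of the three | 2.188 | Φ(2.191 − 1.96) | 59% |
| Readings stop at 12 weeks (one effect) | 1.184 | Φ(2.979 − 1.96) | 85% |

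In the last row only 6 intervention cluster-periods remain, and the last pair's reading has no concurrent control.

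**5. Other correlations, constant effect recalibrated to 90% each time.** Over ρ from 0 to 0.7, R runs from about 1.14 to 1.19, from 2.4 to 2.5, and from 4.9 to 5.4. Power is about 85–86%, 53–56% and 29–31%. For the schedule that stops at 12 weeks it is about 83–85%.

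**6. Other correlations, SD held at 4.05.** At ρ = 0.5 the constant effect has over 99% power, and the Method 3 effects have about 99%, 82% and 50%. The first effect passes 90% from ρ of about 0.15, and the effect on the 12-week schedule from about 0.2.

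**7. If 22 is the community total** (5.5 per period, ρ = 0), the implied SD is about 2.13. The Method 3 effects have 88%, 62% and 36% power, and the 12-week schedule gives 87%.

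The normal approximation with six clusters is optimistic; a small-sample correction would lower all these figures.

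**The case against.** A reader might infer that none of the Method 3 effects can have 90% power on the plan's inputs. The documents do not support that. The SD of 4.05 is back-solved and is not a stated input, and the same people are read repeatedly, so ρ = 0 is the least realistic value. With the SD held at 4.05, a modest correlation lifts the 12-week effect above 90% (step 6). The 6-weekly PHQ-9 readings matter too. With 6-weekly occasions at that SD, the 6- and 12-week effects reach about 90–91%, while longer exposures stay near 67% and 39%. With calibration redone on that layout, power is about 66%, 40% and 23%. Adjustment for the baseline score is also left out of the calculation. This objection stands: the power figures are conditional.

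It is also fair that the primary time point is 12 weeks and that Table 1 ends there. Two or three periods of exposure may never be read, and the weakest figures concern effects for which the article claims no power. If they are not read, Method 3 reduces to one coefficient on this layout, and the remaining gap comes from the schedule. But then the article's reason for choosing Method 3, variation with length of exposure, has little to work on.

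Finally, the first modelling step has no period effect, and without one power is much higher (about 99.8%, 97.5% and 81%). That does not help, since the article itself says that period effects must be controlled.

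An analysis plan may well settle which coefficient is primary. However, the article already fixes both the sized quantity and the method of analysis, and these two differ.

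**Conclusion.** The mismatch is real. The 90% is for one constant effect, the chosen method estimates effects by length of exposure, and the reporting text reads as one contrast. Relative to the sized effect, the variance is about 1.14–1.19 times as large after one period, 2.4–2.5 times after two and 4.9–5.4 times after three. These ratios rest on the four-period layout with period effects, ICC 0.1 and 22 per community per period; they do not depend on the SD and change little with ρ. The corresponding powers hold only if the constant effect has exactly 90%.

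The loss at 12 weeks is small under that calibration and may be absent under other values. The loss at longer exposure is serious. This is not an arithmetic error in the 165, and it does not show that the trial is too small for its 12-week question.

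**What to change.** Name the primary coefficient, and make Sample size, both parts of Statistical analyses and Table 1 agree on it. There are two ways:

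- Make the single-effect, period-adjusted model primary, so that the sized quantity is the tested one, and keep Method 3 as secondary.
- Keep Method 3 as primary and restate the power for its 12-week coefficient, on the schedule that will actually be read, with the SD and within-person correlation stated.

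Do not print 85% as a fixed figure, since it rests on an SD that the article does not give. In either case, state that effects at longer exposure are exploratory and not powered, so that a null there is not taken as a fading effect.

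The cost is a recalculation and possibly a slightly less favourable stated power. No extra participants are needed.
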